### Treatment-related measures

2.12

Treatment-related measures are only administered to the intervention group.

*Therapeutic alliance.* The Working Alliance Inventory-Short Revised (WAI-SR) is used after the iCBT treatment. This instrument measures the therapeutic and collaborative relationship between the coach and the patient. It has shown good psychometric properties specifically for guided internet interventions (Cronbach’s α = 0.93) (49).

*The use of digital content.* The digital platform automatically collects user data on how long the woman spends on the website, which material she uses, and how often she reads it. The frequencies are daily/almost daily, a couple of times a week/once a week, or never. We also examine the proportion of completed coaching calls, the time interval between calls, and the call durations. The woman’s location online and during coaching calls is also recorded, namely, at home, at work, or in another place.

*Treatment satisfaction.* Women who receive the intervention are asked about the general usability and perceived benefit of the intervention after they finish the treatment. In addition, the structured Client Satisfaction Questionnaire for internet-based interventions (CSQ-I) is used. This tool has shown good psychometric qualities and reliability (McDonald’s Ω 0.93–0.95) for assessing general user satisfaction with Web-based interventions for depression (50).

### Randomization and masking

2.13

Randomization is stratified by the study site, and it takes place after the baseline assessment and MINI interview are completed. The study statistician creates the randomization codes separately for each study site using the letters A and B for the intervention and control groups, respectively. The randomization sequences are generated with a 1:1 ratio using the SAS 9.4 computerized random permuted block sequence generator (SAS Institute, Cary, NC, USA) with concealed block sizes. The statistician stays blinded to the treatment groups until the randomization expert opens the coding after the blind review. After each subject is randomized, the platform unlocks the appropriate user interface, and the subjects receive an email telling them what group they are in. The statistician and randomization expert are part of the study team, but they are not directly involved in the conduct of the study.

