### Study type and design

2.1

This study is a two-parallel group RCT. The study subjects and intervention coaches are open to the treatment code, but the statistician and researchers stay blinded until a blind review is conducted for the primary and secondary outcome variables. Blinding is an established approach in clinical trials to minimize the risk of performance and detection bias. Clinical trial guidelines recommend that statisticians remain blinded to allocation prior to the final analysis (25). In this RCT, pregnant women with depressive symptoms are randomized 1:1, by study site, into the *Stronger Together* iCBT intervention with telephone coaching or the educational control group. Both groups also receive standard treatment, according to established regional standard care guidelines, and this may involve therapy and medication. However, ongoing psychotherapy at recruitment is an exclusion criterion (**Table 1**). The study outline is presented in **Figure 1**.

**Table 1 T1:** Inclusion and exclusion criteria.

Inclusion	Exclusion
- Age ≥ 18 years - Fluent in written and spoken Finnish or Swedish - Access to computer or mobile phone with internet/internet literacy - 12–22 weeks pregnant - EPDS score of ≥10 at screening and ≥9 at baseline	- Lifetime history of psychotic disorders, including schizophrenia, schizoaffective disorder, bipolar disorder, and psychotic depression - Active suicidal ideation - Severe substance abuse or dependence - Active ongoing psychotherapy - Already participating in another intervention study to treat the symptoms of antenatal depression - Expecting multiple births

EPDS, Edinburgh Postnatal Depression Scale.

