### Analysis plan

2.16

Statistical analyses will be carried out on the intention-to-treat dataset and repeated for the per-protocol dataset that consists of all evaluable subjects. Categorical variables will be presented as numbers and percentages, and continuous variables as means and standard deviations. Pearson’s chi-square tests or Fisher’s exact tests will be conducted to explore differences in categorical variables between the intervention and control groups at baseline. Two-tailed, two-sample t-tests will be used to explore differences in continuous variables between the groups at baseline. The primary outcome measure is the total EPDS score, which is collected at baseline and 11 weeks after randomization. The follow-up EPDS total scores and changes in EPDS scores will be analyzed using a linear mixed-effects model where the baseline EPDS total score and the stratifying factor study site are included as covariates. The follow-up EPDS total scores and changes in EPDS scores will be analyzed using analysis of covariance (ANCOVA), adjusted for the baseline EPDS total score and stratifying factor study site as a covariate. The secondary outcome measures will be analyzed using the same modelling approach as the primary outcome measure. If feasible, the study subjects will be included as a random effect to generalize the results beyond our study sample. The primary outcome will be analyzed blinded, as the treatment code will only be opened after the study statistician has analyzed the primary outcome. Two-sided significance levels of 0.05 and 95% confidence intervals will be used in statistical testing. The statistical analyses will be carried out using the SAS statistical software (SAS 9.4, SAS Institute, Cary, NC, USA).

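### The blinded primary analysis is not secured as described: the statistician to be blinded creates the lists with A fixed as intervention and B as control, and three sections time the end of blinding differently

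*Protocol article*

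**What the plan says.** All references are to the Protocol article.

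- **Section 2.13 (Randomization and masking), lists:** the trial's statistician "creates the randomization codes separately for each study site using the letters A and B for the intervention and control groups, respectively".
- **Section 2.13, masking:** "The statistician stays blinded to the treatment groups until the randomization expert opens the coding after the blind review". It adds that neither the statistician nor the randomization expert takes a direct part in running the study.
- **Section 2.1 (Study type and design):** "the statistician and researchers stay blinded until a blind review is conducted for the primary and secondary outcome variables". In support it says: "Clinical trial guidelines recommend that statisticians remain blinded to allocation prior to the final analysis".
- **Section 2.16 (Analysis plan):** "The primary outcome will be analyzed blinded, as the treatment code will only be opened after the study statistician has analyzed the primary outcome".
- **Section 2.12 (Treatment-related measures):** "Treatment-related measures are only administered to the intervention group". These are the alliance scale (WAI-SR), the satisfaction scale (CSQ-I), platform use and coaching-call data.

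**The concern.** One person is given two roles that do not fit together without a further step. Whoever writes the lists with a fixed meaning for each letter knows what the letters mean, so that person cannot be blind to groups shown under the same letters. The article also publishes the meaning, and section 2.1 says that the researchers are blinded too. No section says that the letters are re-mapped before analysis, that someone else produces the final list, or that the analysis file uses other labels.

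The stake is limited but real. Participants and coaches know the allocation, and the primary and secondary outcomes are self-reported, so the only masking claimed is that of the statistician and researchers. It protects decisions made during data review and analysis. Section 2.16 still shows some of these: it names both a linear mixed-effects model and ANCOVA for the same outcome, makes a subject random effect depend on feasibility, and defines the per-protocol set by who is evaluable. A separate analysis plan may settle these choices. Until they are settled, blinding is what keeps knowledge of the arms out of them.

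**Working it through.** No arithmetic applies. The check sets the statements side by side.

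**Step 1. Do the letters blind anyone?** That depends on what the file used before opening contains, which the article does not say.

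| Content of the file before opening | Blind to researchers who have read the article? | Blind to the author of the lists? |
|---|---|---|
| Groups shown as A and B, as on the lists | No | No |
| Neutral labels, but with randomization number, date or order | Yes, if they do not hold the lists | No, if a copy of the lists is kept: label patterns can be matched to the sequence within site |
| Neutral labels, without number, date or order | Yes | Largely |
| Any labels, with intervention-only measures included | No: presence of the data marks the arm | No, for the same reason |

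The third row says *largely* because study site must stay in the file as a covariate. If a site's last permuted block is incomplete, its two arm totals can differ, and someone still holding that site's list could compare them. This is why custody of the lists matters as well as the labels.

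The only labels that the article names are those of the first row. The procedure as written therefore does not secure the blinded analysis in section 2.16.

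**Step 2. When does blinding end?**

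- Section 2.1: when a blind review of the primary and secondary outcome variables has been conducted.
- Section 2.13: the randomization expert opens the code after the blind review.
- Section 2.16: only after the primary outcome has been analyzed.

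The article does not define blind review, so there are two readings:

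1. *It is a data review before analysis.* Ending blinding at that point satisfies 2.1 and 2.13 but breaks 2.16. Waiting until after the primary analysis satisfies 2.16, is still after the review as 2.13 requires, and fits 2.1 if its time is taken as a minimum.
2. *It includes the blinded primary analysis.* All three sections then agree.

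The guideline sentence in 2.1 does not decide between them, since it asks only for blinding before the final analysis. The scope also differs: 2.1 names primary and secondary variables, while 2.16 protects only the primary outcome. The sections are thus compatible on one reading and in conflict on another.

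**Step 3. Size.** The documents give nothing from which a bias could be calculated. The affected quantity is the freedom of analysis decisions from knowledge of the arm.

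**The case against.** The strongest defence is that a separate randomization expert opens the code, which implies that something is held back until then: a key, or the link between code and woman. Writing a sequence for a site is not the same as knowing which woman received which entry, and the statistician takes no direct part in running the study. This stands, and it rules out saying that blinding fails.

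A reader might infer that the blinded analysis is simply not delivered, or that one letter gives away the arm of all 634 planned women (2 × 317). The documents support neither. Both need the file used before opening to carry the same A and B as the lists, and no section says that it does.

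It can also be said that opening after the primary analysis is itself after the blind review. That is correct, so the timing is an ambiguity to resolve and not a strict contradiction.

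On the intervention-only data, section 2.1 confines the blind review to primary and secondary outcome variables, and these measures are neither. Nothing says that they are merged into the blinded file, so they are a precaution in the fix and not an error in the plan.

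Finally, an article condenses a fuller protocol. That excuses missing detail on file preparation. It does not excuse a stated procedure that undercuts a stated property: the article itself assigns list creation, and the meaning of the letters, to the person it calls blinded.

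**Conclusion.** The point holds in limited form. As described, the blinded primary analysis is not secured, because the statistician who is to be blinded creates the lists under letters with a fixed and published meaning, and no re-mapping is stated. The three statements on the end of blinding can be reconciled but should give one time.

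This rests on the text as published. If the full protocol already provides for neutral labels and for custody of the lists by someone else, only the wording needs correcting. The consequence is a risk to analysis decisions, without a computable size, and it does not touch the allocation itself. The change should be made, and there is still time: section 2.2 says that recruitment continues.

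**What to change.** 1. **Custody.** The randomization expert, already on the team, holds the lists and the key from now on. The statistician keeps no working copy.
2. **Labels.** For the blinded analysis file, the expert replaces A and B with two neutral labels assigned at random, and alone knows which is which.
3. **Content.** The file omits randomization number, date and order, so that the author of the lists cannot match labels to the sequence. The WAI-SR, CSQ-I, platform-use and coaching-call data stay out until opening.
4. **Timing.** Sections 2.1, 2.13 and 2.16 carry the same rule: the code is opened only after the blind review is complete and the primary analysis is locked. The text should say what the blind review covers, and whether the secondary outcomes are also analyzed before opening.

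The cost is one relabelling step and a restricted variable list in the data export, some time from the randomization expert, and reconciled wording in three sections. No new role, data collection or change to the allocation is needed. If the statistician cannot give up the lists, the small leak through site totals remains and should be acknowledged in the report.

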### Data management

2.14

All the data gathered by the digital platform are stored in a PostgreSQL database (The PostgreSQL Global Development Group). After the collection period has been completed, the data manager will ensure the accuracy of the data and then import the SAS datasets for statistical analysis and reporting. Metadata are stored in spreadsheets, and a data dictionary provides guiding principles for the dataset and variable construction, as well as study-specific information. All datasets from different data sources will be imported to SAS with programs that follow the guidelines in the data dictionary. Code books will be created to document the contents of the SAS datasets: variable names, labels, types, and formats. Quality control procedures such as database auditing, data reviewing, and reconciliation will be implemented to ensure that the statistical analyses use acceptable quality data.

All the baseline questionnaires are filled in online, and participants have to complete all the required fields. The platform does not allow them to select multiple responses to Likert-type questions. During the follow-up phase, participants are given the choice to complete the questionnaires online or on paper versions, which are manually digitized using Microsoft Access (Microsoft Corp., Redmond, WA, USA). To ensure consistency, the online templates follow a similar layout to the paper questionnaires. Personnel digitalizing these follow the guidelines on how to handle unclear answers, such as multiple answers selected. The collected data are stored on the University of Turku file servers, and access is limited to appointed researchers, statisticians, and the data manager. The files are automatically backed up each day and kept for 26 weeks.

### Power

2.15

The aim of the power calculations was to determine how many subjects should be enrolled in the intervention and control groups to achieve 80% power to reject the null hypothesis of equal means. The power calculations were based on a population mean difference of μ1 − μ2 = 9.0 − 10.5 = −1.5 in EPDS scores, with a standard deviation of 6.30 for both groups and a significance level of α = 0.05. This resulted in 278 subjects in both groups. Because we anticipate 14% attrition in both groups, we aim to enroll 317 dyads in both groups. To promote participant retention, each subject will receive reminders by email and telephone from the study coaches. No further data will be collected if a participant chooses to withdraw from the study. If a participant discontinues the intervention but does not withdraw from the study, data will be collected according to the protocol.

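### Enrolling 317 per group and losing 14% leaves about 273, not the 278 that the stated 80% power requires

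*Protocol article*

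**What the plan says.** All the sample size figures are in section 2.15 (Power) of the protocol article. The aim is "to achieve 80% power to reject the null hypothesis of equal means". The assumed effect is "μ1 − μ2 = 9.0 − 10.5 = −1.5 in EPDS scores", "with a standard deviation of 6.30 for both groups and a significance level of α = 0.05". The result is given as "This resulted in 278 subjects in both groups", and the enrolment target follows: "Because we anticipate 14% attrition in both groups, we aim to enroll 317 dyads in both groups".

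Two inputs come from elsewhere. Section 2.16 (Analysis plan) makes the test two-sided: "Two-sided significance levels of 0.05 and 95% confidence intervals will be used in statistical testing". Section 2.13 (Randomization and masking) gives equal allocation: "The randomization sequences are generated with a 1:1 ratio".

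The article prints no formula for the attrition allowance, and it gives no other attrition rate or enrolment target.

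**The concern.** An attrition allowance should ensure that, once the expected losses have occurred, the number the power calculation needs is still there. Attrition is normally a fraction of those enrolled, so the required number is divided by one minus that fraction. Multiplying by one plus the fraction always gives too small a target, and 317 is what multiplication gives here.

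Two things are at stake. First, the sample size statement claims a power that its own assumptions do not deliver. Second, retention will be judged against the 14% figure. Loss between 12.3% and 14% would fall within the declared allowance and still leave fewer than 278 per group. Section 2.2 (Recruitment) says that recruitment is still under way, so the target is still in use.

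**Working it through.** **Inputs.** Difference 1.5, SD 6.30, α = 0.05, power 80%, evaluable number 278, attrition 14% and target 317 (all section 2.15); two-sided test (section 2.16); 1:1 allocation (section 2.13). I read 278 and 317 as numbers per group, because 278 reproduces only on that reading.

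**Step 1: reproduce the 278.** The standardized difference is 1.5 / 6.30 = 0.238.

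- Normal approximation: n = 2 × (1.960 + 0.842)² × (6.30 / 1.5)² = 2 × 7.849 × 17.64 = 276.9, so 277 per group.
- Two-sample t-test with the noncentral t distribution: power is 79.88% at 277 and 80.02% at 278, so 278 per group.
- A one-sided test would need only 219 (normal approximation), so the calculation was two-sided.

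The stated 278 is therefore right, and the problem lies only in the next step.

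**Step 2: reproduce the 317.**

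- Multiplication, n × (1 + d): 278 × 1.14 = 316.92, rounded up to 317. This matches.
- Division, n / (1 − d): 278 / 0.86 = 323.26, rounded up to 324. This does not match.

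That multiplication was used is an inference, since no formula is printed. The next step does not depend on it.

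**Step 3: what 317 delivers.**

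| Quantity | Calculation | Result |
|---|---|---|
| Women per group left after 14% loss | 317 × 0.86 | 272.6 |
| Shortfall against 278 | 278 − 272.6 | 5.4 per group |
| Power at 272 and 273 per group (t-test) | noncentral t | 79.15% and 79.30% |
| Power at 272.6 (interpolated) | 79.15 + 0.6 × 0.15 | 79.2% |
| Largest attrition that leaves 278 | 1 − 278 / 317 = 39 / 317 | 12.3% |
| Target that leaves 278 after 14% loss | 278 / 0.86 | 324 per group, 648 in total |
| Gap in enrolment | 324 − 317 | 7 per group, 14 in total |

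**Step 4: could rounding explain it?** If 14% stood for 13.5%, the target would be 278 / 0.865 = 321.4, or 322 per group, which is still above 317.

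**The case against.** The strongest reply is that the error is too small to matter. The enrolment gap is 7 / 317 = 2.2%, and the power loss is 0.8 of a point. Required numbers scale with the square of the SD, so an SD of about 6.24 instead of 6.30 would close the gap (6.30 × √(272.6 / 277.9) = 6.24). No planning SD or attrition forecast is that precise. This stands as a statement about size.

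A second reply is that the planned analysis in section 2.16 adjusts for baseline EPDS, whereas the power calculation compares unadjusted means. If 6.30 is the unadjusted follow-up SD, a baseline to follow-up correlation of √(1 − 272.6 / 278) = 0.14 would recover the loss. The actual correlation could well exceed that, so it would be wrong to say that the planned primary analysis falls below 80%. However, the article states no correlation and does not use the adjustment in its power statement. Its 80% is for the unadjusted comparison, and for that comparison the figure is missed.

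A third reply is that the 14% might be meant relative to the 278 required (39 / 278 = 14.0%). That would make this a labelling fault and not a wrong target. It is not the usual meaning of attrition in a group, and the sentence would still mislead any reader who compares observed loss with 14%.

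**Conclusion.** The concern holds. With attrition taken as a share of the women enrolled, the printed figures of 278, 14% and 317 cannot all be true. Under the plan's own inputs, 317 per group with 14% loss leaves about 273 and gives 79.2% power for the two-sided unadjusted t-test, against the stated 80%. The target covers 12.3% attrition, not 14%.

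This is a small arithmetic slip in a stated design figure. It does not put the trial's ability to answer its primary question in doubt, and baseline adjustment may more than make up for it, although the document gives nothing from which to quantify that.

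**What to change.** Correct the sentence in section 2.15. The proportionate option is to keep 317 per group (634 in total) and state that this preserves 278 evaluable women per group at up to 12.3% attrition, or that at 14% attrition unadjusted power is about 79%. This costs one sentence and a slightly less favourable figure. If the sponsor wants to rely on baseline adjustment to reach 80%, the sentence should say so and give the assumed correlation.

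The alternative is to keep the 14% and restate the target as 324 per group (648 in total). That means recruiting 14 more women for less than one point of power, and nothing in this check requires it.

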### Analysis plan

2.16

Statistical analyses will be carried out on the intention-to-treat dataset and repeated for the per-protocol dataset that consists of all evaluable subjects. Categorical variables will be presented as numbers and percentages, and continuous variables as means and standard deviations. Pearson’s chi-square tests or Fisher’s exact tests will be conducted to explore differences in categorical variables between the intervention and control groups at baseline. Two-tailed, two-sample t-tests will be used to explore differences in continuous variables between the groups at baseline. The primary outcome measure is the total EPDS score, which is collected at baseline and 11 weeks after randomization. The follow-up EPDS total scores and changes in EPDS scores will be analyzed using a linear mixed-effects model where the baseline EPDS total score and the stratifying factor study site are included as covariates. The follow-up EPDS total scores and changes in EPDS scores will be analyzed using analysis of covariance (ANCOVA), adjusted for the baseline EPDS total score and stratifying factor study site as a covariate. The secondary outcome measures will be analyzed using the same modelling approach as the primary outcome measure. If feasible, the study subjects will be included as a random effect to generalize the results beyond our study sample. The primary outcome will be analyzed blinded, as the treatment code will only be opened after the study statistician has analyzed the primary outcome. Two-sided significance levels of 0.05 and 95% confidence intervals will be used in statistical testing. The statistical analyses will be carried out using the SAS statistical software (SAS 9.4, SAS Institute, Cary, NC, USA).

